## Discussion

The addition of contingent incentives to standard evidence-based smoking cessation treatment in opiate addiction clients will be an innovative approach, having never been attempted before in the UK.

The current trial has a number of limitations that should be improved in future studies. First, the value and frequency of rewards in this study are comparatively lower than those of previous trials and should, therefore, be increased to encourage the cessation. The use of breath CO only in measuring abstinence is not the most rigorous method available for testing, due to the relatively short period of time it takes for breath CO levels to return to levels considered as those of a non-smoker. Urine cotinine levels provide a more rigorous measure of abstinence; however, they are confounded by the use of NRT, therefore necessitating the measurement of anabasine instead. The measurements of both cotinine and anabasine were beyond the scope of the current intervention. Furthermore, provision of incentives to participants in the attendance group should come before breath CO levels are measures to avoid the risk of these participants thinking their incentives are linked to CO levels.

However, the intervention has a number of potential strengths. If feasible, the intervention will be easily disseminated, and it has the potential to be an effective intervention for smoking in this client group. Pilot studies are an imperative step in the development of complex interventions, and form the first step on the road to full-scale RCT and potentially implementation.^32 33^ If successful, this programme paves the way for the development of a full-scale RCT of CM for smoking in opiate addiction treatment, which would include an economic evaluation, and potential trials for smokers in other drug addiction treatment.

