### CM intervention

The CM intervention will run as an adjunct to the normal smoking cessation treatment, and follows an escalating with reset schedule. In escalating with reset CM, rewards increase in a set increment value for each successive verified display of the desired behaviour. When the desired behaviour is not observed, no reward is given, and the reward value for the next verified display of the desired behaviour is reset to that of the initial reward. Reward values then begin to rise again in the same way as before. The CM intervention will run for 5 weeks in total, starting in week 2 of the standard stop smoking services treatment and ending in week 6 (table 1). Randomisation will be performed after collection of demographics following taking of consent. Participants will be rewarded for smoking abstinence in the experimental condition, or for attending the smoking cessation clinic in the control condition. Smoking abstinence will be defined as a breath CO reading of <10 ppm, and attendance will be defined as attending the smoking cessation treatment at the clinic that week. After each smoking cessation treatment session, the cessation worker will fill out a slip that records each participant’s individual participant number and his or her breath CO for that day. The cessation worker will give these slips to the PI who will sit in an adjacent room and administer rewards where appropriate. All participant data will be recorded using participant numbers ensuring that no identifiable data leave the clinic, and will be stored in an encrypted file, separate to a sheet matching participant names to IDs which will be kept in a locked office at the treatment centre. Due to the nature of the CM intervention, it is not possible to blind participants to treatment allocation. Cessation workers will not be made aware of treatment allocation; however, they cannot be considered to be blinded to treatment allocation as it is possible that clients may discuss this with them.

**Table 1 T1:** Reward schedule

Smoking cessation treatment week No	1	2	3	4	5	6
CM week No		1	2	3	4	5
Reward value	£0.00	£5.00	£10.00	£20.00	£40.00	£40.00

Reward schedule for a participant that remains abstinent and/or attends all smoking cessation treatment meetings (dependent on condition) for the duration of the intervention. Maximum total reward: £115.

CM, contingency management.

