Reward values will be the same in both conditions and begin at £5, doubling each time the incentivised behaviour is recorded to a maximum of £40. All rewards will be given as ‘Love2Shop’ vouchers. Over the course of the whole intervention, participants will be able to earn a maximum of £115 (table 1). At the end of the CM intervention, participants will be asked to complete a client satisfaction and well-being survey, which was previously used to assess client satisfaction of stop smoking services treatment.^31^

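### Attendance-arm vouchers are paid after the CO reading has gone to the payer, a weakness the protocol acknowledges but leaves uncorrected, and it could dilute the secondary smoking comparison by an unknown amount

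*Protocol article*

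**What the plan says.** The CM intervention section of the protocol article describes a single payment route. After each session the cessation worker completes a slip with the participant number and "his or her breath CO for that day". Then "The cessation worker will give these slips to the PI who will sit in an adjacent room and administer rewards where appropriate". No separate route or earlier payment is described for the attendance condition.

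The conditions differ in what earns the voucher. In the experimental condition, "Smoking abstinence will be defined as a breath CO reading of <10 ppm". In the control condition, "attendance will be defined as attending the smoking cessation treatment at the clinic that week". The amounts do not differ: "Reward values will be the same in both conditions and begin at £5, doubling each time the incentivised behaviour is recorded", up to £40 per session and £115 in total. Participants are not blinded; the section states that "it is not possible to blind participants to treatment allocation".

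Among the weaknesses of this trial that it wants later studies to put right, the Discussion says that "provision of incentives to participants in the attendance group should come before breath CO levels are measures", and gives the reason: "to avoid the risk of these participants thinking their incentives are linked to CO levels".

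Under Planned analysis, smoking cessation is compared between conditions by a two-sided χ² test at 0.05, as a secondary objective. The primary outcome, completion of the five weeks, is reported descriptively.

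**The concern.** Because voucher values and the payment route are the same in both conditions, what separates the arms is the behaviour that earns the voucher. A control participant blows into the CO monitor, the reading goes on a slip, the slip goes to the person holding the vouchers, and a voucher follows. An abstinent participant in the experimental condition goes through the same sequence. A control who concludes that the reading decides payment is partly exposed to the experimental contingency, and the smoking comparison then moves towards no difference.

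That comparison is secondary and preliminary, but the Discussion presents a full-scale trial as the next step. An estimate diluted in this way could mislead its planning. The Discussion explains why cotinine and anabasine were not measured (they were beyond the scope of the study). It gives no such reason for leaving the payment order unchanged.

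**Working it through.** **1. The two sections side by side.**

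| Question | CM intervention section | Discussion |
|---|---|---|
| What is described? | What is done in this trial | What later studies should improve |
| Order for the attendance arm | CO on slip, slip to PI, voucher | Voucher before CO |
| Risk named? | No | Yes: controls may link vouchers to CO |

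The first column is the operating procedure. The second is a comment on it. Both can be true together, so the finding is an uncorrected weakness and not a contradiction.

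**2. Rewards are equal across conditions.** The reward table gives 5 + 10 + 20 + 40 + 40 = £115, which reproduces the stated maximum, and the text applies it to both conditions. Reward size therefore does not separate the arms.

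**3. Dilution, as an illustration only.** The protocol gives neither expected quit rates nor a rate of mistaken belief, so it has no figure of its own to reproduce here. Assumptions:
- 20 participants per arm (40 recruited, equal allocation assumed)
- a share f of controls responds exactly as if paid for abstinence
- assumed quit rates p_T (CM for abstinence) and p_C (CM for attendance)

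Diluted control rate: p_C* = p_C + f(p_T − p_C). Diluted difference: Δ = p_T − p_C* = (1 − f)(p_T − p_C).

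Power is the normal approximation for two proportions, two-sided α = 0.05: Φ[(Δ − 1.96·SE₀)/SE₁], with SE₀ = √(2p̄(1 − p̄)/20), SE₁ = √((p_T(1 − p_T) + p_C*(1 − p_C*))/20) and p̄ the mean of the two rates.

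| f | 30% vs 10%: control rate | Difference | Power | 50% vs 10%: control rate | Difference | Power |
|---|---|---|---|---|---|---|
| 0 | 10% | 20 points | 35% | 10% | 40 points | 81% |
| 10% | 12% | 18 points | 28% | 14% | 36 points | 70% |
| 25% | 15% | 15 points | 20% | 20% | 30 points | 51% |
| 50% | 20% | 10 points | 11% | 30% | 20 points | 25% |

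In the 30% vs 10% case the extra control quitters are 20 × 0.02 = 0.4, 20 × 0.05 = 1 and 20 × 0.10 = 2 people.

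**4. What limits f.** Controls know their condition. A control who attends with CO of 10 ppm or more has still shown the rewarded behaviour, so is paid, and the next attendance earns twice as much until the £40 cap. A smoking control who attends even once therefore sees that the reading did not decide payment. The formula ignores this correction and gives a mistaken control the full experimental effect, so for any given initial share of mistaken controls the table is nearer an upper bound than an expectation. The correction does not reach a control who stays away, or one whose readings are always below 10 ppm.

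**The case against.** The strongest reply is that the authors have already said this. The Discussion names the payment order, the risk and a remedy, and a pilot whose primary objective is to find what needs changing before a full trial has done its job by naming it. The affected comparison is secondary, in a sample deliberately not sized for efficacy, and with assumed rates of 30% and 10% its power is only about 35% before any dilution. Unblinded controls who are paid while still smoking will largely correct the belief. The participant information sheet and the satisfaction questionnaire are not shown, so neither can be called deficient.

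Most of this stands, and it limits the point. A reader might infer three stronger things that the documents do not support:
- **That the protocol contradicts itself.** The Discussion sentence is framed as a limitation for later studies, not as an instruction for this one.
- **That the contrast is diluted by a known amount.** Every rate in the illustration is assumed.
- **That control completion will fall because smoking controls stay away.** This is conceivable, but nothing in the protocol supports it.

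Paying controls before the CO test is also open to argument as a change within this trial. It could reward attendance before the session is complete, and it would handle the arms visibly differently although cessation workers are not told the allocation.

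What does not stand is that naming the risk is enough. The pilot can reduce it and measure it at almost no cost, which serves its own primary objective better than an untested remark.

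**Conclusion.** The weakness is real and rests on the protocol's own words: attendance-arm vouchers follow a CO reading that has been passed to the payer, and the authors accept that this may lead controls to think payment depends on CO. The likely direction is towards no difference in the secondary smoking-cessation comparison. The difference shrinks by the factor 1 − f, where f, the share of controls who respond fully as if paid for abstinence, is not known and is held down by unblinding and by payment at 10 ppm or above. For f between 10% and 50%, an assumed 20-point difference becomes 18 to 10 points and an assumed 40-point difference becomes 36 to 20 points. These figures assume 20 per arm and the stated quit rates, none of which the protocol gives. The documents support no conclusion about an effect on the primary outcome. A correction is worth making because it is cheap, not because the bias has been shown to be large.

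**What to change.** - **Procedure.** Keep the current session order. At each attendance-arm payment the PI states, in fixed wording, that the voucher depends on attendance only and not on the CO reading.
- **Measurement.** Check the satisfaction questionnaire already planned for the last day of participation. If it does not ask what the participant believed the vouchers were for, add one item that does. Report the answers by condition and use them in interpreting the cessation comparison. Participants who leave early may not complete it, so give the number answering in each arm.
- **Timing.** The trial was registered retrospectively, so recruitment may be under way. If so, apply the change to the remaining participants and record the date. If none remain, carry the dilution risk into the interpretation of the cessation comparison.

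The cost is a few seconds per payment and one questionnaire item, with no extra staff or visits. A change part-way through means that earlier and later controls were paid under slightly different wording, which is why the date must be recorded.
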